### Statistical analysis

#### Sample size

Previous studies (30) have shown that a combined program of exercise and cognitive training for 3 months can improve working memory in cognitively healthy older adults, with an approximate effect size of 0.9. Considering the characteristics of our study and using GPower software, we calculated that a sample size of 21 participants per group would be needed to achieve a power of 0.8, with an alpha of 0.05 and a beta of 0.2. Assuming a dropout rate of 15%, a final sample size of 24 participants per group would be required for the efficacy and feasibility study. The sample size for the implementation study will be calculated based on the results of the previous phase.

#### Analyses of outcomes

After measurements, participants’ data will be entered into a database by two independent researchers. Blinding on handling data will be assured by separating measurement values from general participant information.

The statistical analysis plan can be summarized as follows: (i) after checking that randomization has been effective, we will winsorize the variables to limit the influence of extreme values; this will be done by replacing values below the 1st percentile with the 1st percentile value and those above the 99th percentile with the 99th percentile value. (ii) Mixed regression models will be used in which each outcome variable will be the dependent variable, interventions will be treated as fixed effects (1 = IG and 0 = CG), and the models will be adjusted for baseline reference values and age. The results will be expressed as absolute differences in changes in the variables between baseline and final measurement. When the dependent variable is dichotomous, odds ratios (ORs) will be calculated. Finally, (iii) analyses will be conducted from an intention-to-treat perspective, whereby participants will remain in the group to which they were originally assigned, regardless of the degree of compliance with the intervention.

The results will be considered statistically significant when *p* < 0.05. The analyses will be performed using STATA16.

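### Winsorizing at the 1st and 99th percentiles does little or nothing with 48 participants, so the outlier protection the plan states is largely or wholly absent in the efficacy phase

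*Protocol article*

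**What the plan says.** The section on analyses of outcomes opens its summary of the analysis plan with this step: after a check of the randomization, "we will winsorize the variables to limit the influence of extreme values". The rule is "replacing values below the 1st percentile with the 1st percentile value and those above the 99th percentile with the 99th percentile value". The mixed models, adjusted for baseline value and age, follow. Stata 16 is the named software. The article does not say which percentile definition applies, or whether percentiles are taken per arm, over both arms, or over both visits.

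The sample size section states that "a sample size of 21 participants per group would be needed to achieve a power of 0.8", based on an earlier study "with an approximate effect size of 0.9", and that after allowance for dropout "a final sample size of 24 participants per group would be required for the efficacy and feasibility study". The size of the later implementation phase is left open.

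**The concern.** A percentile limit can only act on values that lie beyond it. When 1% of the sample is less than one observation, there may be no such value, and the most extreme observation then sets its own limit. The rule, its purpose, the software and the sample size are all stated in the article, and they do not fit together.

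At stake is how far the efficacy result can be trusted when one measurement is unusual. Each arm has about 20 people, and the executive-function endpoints include an attention score built partly on reaction time, so an extreme value is plausible. A reader of the methods would take the models to be guarded against such a value when they are close to, or the same as, models with no guard.

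**Working it through.** **Inputs.** Sample size section: effect size 0.9, alpha 0.05, power 0.80, 21 per group, 15% dropout, 24 per group. Analyses of outcomes: limits at 1% and 99%, Stata 16. Assumed: two-sided testing, and the percentile definitions below.

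**The plan's own figure.** A two-sided two-sample t-test with d = 0.9, alpha 0.05 and power 0.80 needs 20.4, so 21 per group (power 0.812). For dropout, 21 × 1.15 = 24.15, which gives the stated 24; 21 / 0.85 = 24.7 would give 25. The difference does not matter here. The sample is 2 × 24 = 48 enrolled, with 2 × 21 = 42 needed for analysis.

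**Rank-based percentile (taken as Stata's default).** Let P = n × p / 100. The percentile is the first ordered value whose rank exceeds P, or the mean of two neighbours if P is a whole number.
- n = 48: for p = 1, P = 0.48, which gives the minimum. For p = 99, P = 47.52, which gives the 48th value, the maximum. Nothing lies outside, so 0 values are replaced.
- n = 42: P = 0.42 and 41.58, again minimum and maximum; 0 replaced.
- One arm (n = 24) or both visits pooled (n = 96): 0 replaced.
- The rule first acts at n = 100, where one value per tail changes.

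The alternative based on (n + 1) gives the same counts. At n = 48, 1% of 49 is 0.49, below rank 1; 99% of 49 is 48.51, above rank 48.

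**Other definitions.** Of nine standard quantile definitions tried at n = 48, seven replace nothing and one alters only the maximum. The ninth, linear interpolation, puts the limit (n − 1) × 0.01 = 0.47 of the way from the extreme value to its neighbour, so one value per tail moves 47% of that distance. Example: 47 standard normal values with a second-largest of 2.12, plus one value of 10. The rank-based rule leaves it at 10. Linear interpolation gives 10 − 0.47 × (10 − 2.12) = 6.3. The most favourable reading combines linear interpolation with pooling of both visits (n = 96): the fraction is 95 × 0.01 = 0.95, so a lone outlier would be nearly contained. It still covers only one value per tail.

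**Illustration only: what one unhandled outlier can do.** Simulated trials with 20 per arm, true d = 0.9 and an unadjusted t-test; calculated power without an outlier is 0.79. One control value is set 5 SD from the control mean, which shifts the difference by 5 / 20 = 0.25.

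| Outlier in control arm | Analysis | Mean estimate | Power |
|---|---|---|---|
| 5 SD high | no winsorizing | 0.65 | 0.29 to 0.32 |
| 5 SD high | rank-based 1%/99% | identical | identical |
| 5 SD high | linear-interpolation 1%/99% | 0.68 to 0.70 | 0.41 to 0.43 |
| 5 SD high | Huber regression | 0.82 | 0.67 |
| 5 SD low | no winsorizing | 1.15 | 0.86 |

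Ranges are across repeated runs. With no true effect and the outlier placed at random, the type I error was about 0.046.

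**The case against.** Four points on the other side have weight.

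- *The percentile definition is not given.* This stands. To say the rule cannot act at all would go beyond the article; under linear interpolation it acts a little. Most definitions, including the ones taken here for the named software, leave every value unchanged.
- *An inert step harms nothing.* This also stands for bias: no estimate is distorted and no test invalidated. It does not rescue the stated purpose.
- *The power loss in the illustration is not caused by the rule.* Correct. A reader might infer from the fall to about 0.3 that the plan damages the trial. It does not: any least-squares analysis without outlier handling behaves that way, an outlier on the other side raises the estimate, and an arm-blind outlier does not inflate false positives. The example uses an unadjusted test rather than the planned adjusted model. It also fits the MMSE poorly at the upper end: the score stops at 30 and entry generally requires more than 24, so with a mean of 25 or more a value 5 SD high would need an SD of 1 or less.
- *Other safeguards exist.* Two independent researchers enter the data, and the recruitment and allocation section lets the separate databases be crossed to detect abnormal values during measurement. These may catch errors. They do not limit the influence of a genuine but extreme value.

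A further inference would be that in the implementation phase the rule overwrites valid data to real effect. The article does not support that. It leaves that phase's size open, and replacing tail values whether or not they are errors is what winsorizing does by design. At an illustrative n = 300 and d = 0.40, the estimate moved from 0.402 to 0.396 and power from 0.936 to 0.935.

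**Conclusion.** The point holds for the efficacy phase. With 48 enrolled and 42 needed for analysis, 1% is less than half a person. Under rank-based percentiles no value is replaced; under linear interpolation at most one per tail is partly pulled in. The outlier protection that the article states is therefore largely or wholly absent where the sample is smallest.

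The count rests on the article's own sample size and limits, plus an assumed percentile definition. It does not rest on the 5 SD example, which shows only that unhandled outliers can matter in either direction. The full analysis plan is not shown and may hold a robust or unwinsorized analysis; its absence from the article is not part of this point. This should be corrected before analysis, but it does not invalidate the planned test.

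**What to change.** For the efficacy phase:

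1. Do not present 1%/99% winsorizing as protection against extreme values.
2. Make the main analysis the recorded values, after outlying entries have been checked against source by staff who do not know the group. The existing data-entry and abnormal-value procedures can carry this.
3. Prespecify one sensitivity analysis per primary endpoint that works at this size: for example a Huber or MM robust regression with the same baseline and age adjustment, or winsorizing with limits that bind at n = 48, labelled as sensitivity. If winsorizing is chosen, state the percentile definition and the set of values over which percentiles are taken.

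The cost is a change of wording and one more model and reported result per primary endpoint. Recruitment and data collection are unaffected.

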### Qualitative approach

A qualitative study will be carried out following Giorgi’s phenomenological approach with the aim of describing the meanings of phenomena from participants’ experiences (31, 32). The information obtained from the qualitative study on barriers to and facilitators of the implementation of the cognitively demanding physical exercise intervention using eHealth for older people will be used to adapt the MOVI-ageing application.

Focus groups will be used because of their capacity to generate in-depth information on the perceptions and opinions of the phenomenon through the interaction of the participants and to explore a wide variety of opinions on the subject (33). Giorgi’s descriptive phenomenology approach will be used to explore the barriers and facilitators of older people’s use of a computer application for physical exercise, information that will guide the development and implementation of the MOVI-ageing intervention (31). As a data collection technique, focus groups will be conducted in a purposive sample of homogeneous groups of older people of both genders (men and women), socioeconomic level (low, medium, high), educational level (university or intermediate level studies, school graduate, no studies) and physical condition (assessed with the SF-12 scale). The criteria of intragroup homogeneity and intergroup heterogeneity will be followed to ensure that participants can express themselves freely.

The focus groups will be conducted by experts in qualitative methodology who will share a common protocol that will include the methodology of data collection and the script of topics. Each focus group will have a moderator, who will have the script of themes, conduct the focus group, and launch the questions, and another researcher who will act as an observer. The focus groups will be conducted in a neutral, comfortable, quiet, and private place, will last between 60 and 120 min, will be audio-recorded after obtaining the participants’ permission, and will include between 5 and 8 participants per group. At least two focus groups will be conducted, but the final number will be conditioned by the data saturation criterion to be reached when no novel analytic information is obtained (34).

Data collection and analysis will follow an interactive circular process so that the data collected in each focus group will serve to refine the topic script of the following groups. In addition, all data will be compared to each other through the constant comparison method. As data verification strategies, the focus groups will be audio-recorded and transcribed verbatim and subsequently anonymized for analysis. In addition, the interview transcripts will be returned to the participants for their agreement with the interviews. During the analysis phase, data will be grouped into themes and subthemes following the following steps of Giorgi’s phenomenological approach: (1) collect and describe phenomenological data, (2) read the full description in the transcribed texts, (3) break descriptions into meaning units that are as descriptive as possible, avoiding precocious interpretation of the results, (4) group the units by common meanings, forming clusters of meanings, and (5) interpret the clusters of meanings and identify the themes that will show the meaning of the phenomenon (31). Two researchers with expertise in qualitative methodology will independently perform the data analysis, subsequently agreeing on the results; in case of disagreement, a third researcher will mediate. The triangulation of data by three researchers will allow the emergence of different perspectives and deepen the analysis, increasing the validity of the findings. Atlas-ti 9.0 software will be used as an aid during this phase. The credibility, transferability, reliability or dependability, and confirmability criteria of Guba and Lincoln will be followed to ensure the reliability of the study (35, 36).

## Discussion

Physical exercise stimulates neuroplasticity processes, producing effects on brain structure, function, and connectivity. Exercise causes a change in the metabolic activity of the brain, increasing cerebral blood flow resulting in increased oxygen and glucose metabolism, as well as promoting cardiovascular function and thus reducing peripheral cardiovascular risk factors (e.g., hypertension) for cognitive impairment (37–40). Improved cognitive performance has also been linked to several growth factors whose expression is related to physical exercise, such as insulin-like growth factor 1 (IGF-1), which promotes neuronal growth and improves cognitive performance, and vascular endothelial growth factor (VEGF), which stimulates angiogenesis and vasculogenesis and promotes tolerance to cerebral ischemia (41, 42).

In addition, physical exercise activates BDNF (43), which plays a crucial role in neuroprotection and synaptic plasticity by promoting neurogenesis, cell proliferation, and synaptogenesis in the hippocampus, as well as angiogenesis in other brain areas (44, 45). Finally, exercise contributes to improving memory by elevating dopaminergic activity in the basal ganglia and elevating blood concentrations of other biomarkers (norepinephrine, lactate, etc.) and reduces inflammatory cytokines and oxidative stress, suggesting anti-inflammatory and antioxidant effects in the brain (46, 47).

Considering the benefits of physical exercise for older individuals, it does not seem a good practice to avoid prescribing physical exercise for these individuals. Despite this, physical exercise recommendations have not been fully integrated into primary or geriatric medical practice and are almost absent in the basic training of most health professionals (48). One of the main reasons is the lack of specific tools and recommendations, as even the WHO does not distinguish in its physical activity recommendations between different specific conditions among older people.

Although previous experiences are an important source of evidence, we still lack interventions that are applicable, suitable for all people regardless of gender, and supported by a user-friendly platform. Interventions are needed that include behavior modification models, including active participant learning, intrinsic motivation, self-awareness, and learning over time (49). In addition, these interventions should be culturally adapted and based on individual preferences, accessible to large population groups at low cost, and easily reproducible, including ongoing and personalized support advice. In view of the above, it seems necessary to evaluate the effectiveness of a cognitively demanding cognitive physical exercise home-based eHealth intervention from a population perspective.

This study has some limitations that should be recognized. Although this is a randomized controlled trial, it will not be possible to blind participants to the allocation group, and some bias could be derived from this fact. Second, the measurements and intervention program sessions will be standardized by training the staff, but some variability could not be neglected. Finally, a program based on physical activity will be designed without considering diet interventions, although adherence to Mediterranean diet will be collected, other diet behavior information will not be available.

## Implications

The results of this project aim to impact in the QoL and the well-being of a specific group of population with the objective to cover their needs. The implementations of the findings and their inclusion in guidelines, may directly impact in older people’s life and relatives, through the prevention of morbidity and the reduction of years lost to disability. These benefits may be reflected in the reduction of economic expenditure by reducing the demand for social and health care services.

## Strengths and limitations of this study

Cognitively demanding physical exercise has been proposed to foster cognitive function regardless of age.

This study aims to describe the protocol of a home-based eHealth cognitive-demanding exercise intervention for older adults in cognitive and physical function.

The inclusion of patients in the design of interventions allows them to culturally adapt to individual preferences and improve the participants’ adherence.

The development of the eHealth intervention in two phases and the inclusion of the qualitative approach will ensure the adaptation of the intervention to users’ preferences.

## Ethics statement

The studies involving humans were approved by the Clinical Research Ethics Committee of the ‘Virgen de la Luz’ Hospital in Cuenca approved the study protocol (registration number: 2022/PI3222). The studies were conducted in accordance with the local legislation and institutional requirements. Written informed consent for participation was required from the participants or the participants’ legal guardians/next of kin in accordance with the national legislation and institutional requirements.

## Glossary

BDNF: brain-derived neurotrophic factor
BMI: Body mass index
cAIx: central augmentation rate
CG: Control Group
COREQ: Consolidated Criteria for Reporting Qualitative Studies
DCCS: Dimension Change Card Sort
ELISA: Enzyme-linked immunosorbent assay
FES-I: Efficacy Scale International
GDS: Geriatric Depression Scale
HRQoL: Health-related Quality of Life
IFCC: International Federation of Clinical Chemistry and Laboratory Medicine
IG: Intervention Group
IGF-1: insulin-like growth factor 1
MEDAS: Mediterranean diet adherence screener
MMSE: Mini-Mental State Examination
NGSP: National Glycohemoglobin Standardization Program
OR: odds ratio
PSQI: Pittsburgh Sleep Quality Index
QoL: Quality of Life
rAIx: radial augmentation rate
SF-12: 12-Item Short Form
SPPB: Short Portable Physical Battery scale
WHO: World Health Organization
6MWT: 6-minute walking test
